## 3.7 Baseline Evaluation:

At enrollment before baseline evaluation begins, and at all country sites, participants will be assigned a unique study number that will be used on all study forms. The study participant number will take the following format.

Country code

Facility/ cluster code

Participant

number

Study arm code

AA

**-**

#

**-**

#

#

#

#

#

**-**

The study number will be used to identify the study participant at each study visit, and will be used on all study data collection forms, on biochemical sample test requisition and results forms, as well as in the databases.

Following enrollment and study number assignment, participants in all the trial arms will under-go a baseline evaluation that will comprise the following:

1. Recording of the participant’s contact information to be used to contact the participant in case they fail to report back to the health facility for their clinic and/or study visits,
2. A background information that will collect demographic and social characteristics
3. Behavioral risk factor characteristics (physical activity, tobacco and alcohol use history, and dietary behavior assessment).
4. Medical history assessment
5. Physical measurements (weight, height, waist circumference and blood pressure),
6. Biochemical measurements including HbA1c and FPG (Uganda & South Africa only)
7. A 7-day pedometer steps assessment
8. Participant diabetes knowledge
9. Illness perception
10. Social support and sources of support
11. Self-efficacy, autonomy support & self-regulation
12. Psychological adjustment
13. Quality of life & Stress
14. Adherence to study procedures and to intervention elements

***Facility baseline evaluations:***

We will conduct baseline facility evaluations that will include:

1. Health facility assessment on the level of staffing with different health care cadres, equipment and supplies, and availability of guidelines relevant for diabetes care
2. A context assessment to assess the opinion and views of facility health care workers regarding facilities in their working environment

***Community evaluations:***

Furthermore as part of baseline evaluation, we will conduct community environment evaluation (EPOC)

## 3.8 Follow-up evaluations:

Each participant will be followed up to 12 months from the time of enrollment, or until his/her death or loss to follow-up. Active data collection will occur at baseline and months 3, 6 and 12. However participants with diabetes will return to their respective cluster health facilities monthly for their clinic visits and drug refills.

During follow-up study visits, we will conduct the following assessments:

1. Medical history assessment
2. Clinical evaluation of participants to assess any changes in clinical participants markers and outcomes
3. Physical measurements (weight, waist circumference and blood pressure),
4. Biochemical measurements including HbA1c and FPG (Uganda & South Africa only)
5. 7-day pedometer steps assessment
6. Participant diabetes knowledge
7. Illness perception
8. Social support and sources of support
9. Self-efficacy, autonomy support & self-regulation
10. Psychological adjustment
11. Quality of life & Stress
12. Diabetes treatment satisfaction
13. Adherence to study procedures and to intervention elements
14. Out of pocket expenditure and incremental cost on the system
15. Incremental cost to the health facility
16. Process evaluation

***Process Evaluation***: In any trial, a high degree of compliance to the intervention elements is necessary to minimize decrease in statistical power and obtain unbiased results. In the case of non-compliance that is associated with both intervention element(s) and the study outcomes of interest, there is a particularly serious threat to validity. However, the best method for ensuring full compliance is to monitor compliance with the trial processes. Thus, participants will receive encouragement at their monthly visits to take their medications at the same time every day, and identify a Care Companion to provide medication reminders, as well as healthy lifestyle adherence. Research nurses will assess compliance in three ways: direct questioning and pill count assessed at each monthly visit, and biochemical assessment of plasma glucose. Research nurses will also make an effort to identify and address barriers to compliance.

Table 15 summarizes the schedule of study procedures and tools to be applied.

Table 15: Schedule of study procedures

| **Study Activity** | | **-7 to 0 days** | **BASELINE** | **M3** | **M6** | **M12** |
| --- | --- | --- | --- | --- | --- | --- |
| **I. Consent forms** | Screening consent | X |  |  |  |  |
|  | Study informed consent |  | X |  |  |  |
|  |  |  |  |  |  |  |
| **II. Enrollment & Study ID** | Study ID number assignment |  | X |  |  |  |
|  | Patient registration in Register |  | X |  |  |  |
|  | Patient file creation |  | X |  |  |  |
|  | Patient appointment card |  | X |  |  |  |
|  |  |  |  |  |  |  |
| **III. Physical Measurements** | Height |  | X |  |  |  |
|  | Weight |  | X | X | X | X |
|  | Waist circumference |  | X |  | X | X |
|  | Blood pressure |  | X | X | X | X |
|  | 7-day pedometer steps |  | X |  |  | X |
|  |  |  |  |  |  |  |
| **IV. Biochemical** | FPG (Uganda & South Africa) | X, X | X | X | X | X |
|  | HbA1c (All sites) |  | X |  |  | X |
|  |  |  |  |  |  |  |
| **V. Basic participant data** | Pre-eligibility assessment | X |  |  |  |  |
|  | Eligibility confirmation |  | X |  |  |  |
|  | Eligibility and recruitment check |  | X |  |  |  |
|  | Contact Information |  | X |  |  |  |
|  | Demographic and social measures |  | X |  |  |  |
|  | Medical and medication history |  | X |  |  |  |
|  | Behavioral measures (diet, physical activity, foot care, tobacco use, alcohol consumption) |  | X |  |  | X |
|  |  |  |  |  |  |  |
| **VI. Intervention process measures** | Participant diabetes knowledge |  | X |  |  | X |
|  | Illness perception |  | X |  |  | X |
|  | Social support and sources of support |  | X |  |  | X |
|  | Self-efficacy, autonomy support & self-regulation |  | X |  |  | X |
|  | Psychological adjustment |  | X |  |  | X |
|  | Quality of life & Stress |  | X |  |  | X |
|  | Diabetes treatment satisfaction |  |  |  |  | X |
|  | Out of pocket expenditure |  |  | X | X | X |
|  | Incremental cost to the health facility |  |  | X | X | X |
|  | Adherence to study procedures and to intervention elements |  | X |  |  | X |
|  |  |  |  |  |  |  |
| **VII. Facility forms** | Process evaluation |  |  | X | X | X |
|  |  |  |  |  |  |  |
| **VIII. Community forms** | Environment context measurement (EPOC) |  | X |  |  |  |

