2. Contacting participants’ care companion by telephone if the patient was unreachable or failed to visit the clinic after being contacted on their mobile phone.

Patient flowchart from the clinical guidelines will be printed and displayed in the health facilities to guide both the participants and the health workers. A health worker will guide patients through the process. Separate flowcharts will not be provided for the patients, as most people in the study area are illiterate.

Motivational coaching will only be delivered in groups at months 3, 6, 12 & 18 at the study follow up visits. Motivational coaching guideline will give special tools for addressing those who are non-adherent to medication and those with poorly controlled blood glucose.

Self-monitoring will involve only monitoring of blood sugar using glucometer. Other measurements including weight, height and waist circumference will be done at the health facility during the follow up visits

Table 5: Elements of Minimum Level of Quality Care as Implemented in the Health Facilities Across the SMART2D Sites

| **FACILITY**  **STRATEGIES** | | **KEY ELEMENTS** | **South Africa** | **Sweden** | **Uganda** |
| --- | --- | --- | --- | --- | --- |
| **1. Organization of care process** | | a. Available and functioning minimal infrastructure adequate | Pre-existing but standardized for trial:   - Glucometers & strips - Automatic BP machines - Weighing scales - Stadiometers - Measuring tapes | Pre-existing but standardized for trial:   - Glucometers & strips - Automatic BP machines - Weighing scales - Stadiometers - Measuring tapes | By SMART2D:   - Glucometers & strips - HbA1C analyser & test kits - Automatic BP machines - Weighing scales - Stadiometers - Measuring tapes - Medicines to cover stock out |
|  |  | b. Guidelines and task identification | Pre-existing:   - PACK guidelines for health workers at primary care level   By SMART2D:   - Patient flow chart | Pre-existing:   - Clinical guidelines for T2DM, overweight and obesity, and healthy lifestyle   By SMART2D:   - Screening algorithm - Patient flow chart | By SMART2D:   - Clinical guidelines, including task shifting guidelines - Clinical treatment algorithm posters - Patient flow chart |

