## 3.9 Outcomes of interest:

*Primary outcomes of interest*

Among participants with pre-diabetes, the primary outcome of interest will be reduction in plasma glucose between baseline and month 12 of follow-up. We hypothesize that participants with pre-diabetes in the facility + community arm will on average have a higher reduction in their HbA1c reading by the end of follow-up compared to participants with pre-diabetes in the facility alone arm, and the current practice arm in Uganda.

Regarding participants with type 2 diabetes, research has shown that, reduction of HbA1c level by 1% among such individuals leads to: a) 19% less likelihood of cataracts, b) 16% less likelihood of heart failure, and c) 43% less likelihood of amputations or death due to peripheral vascular disease [Anon 1993]. Further the UK Prospective Diabetes Study (UKPDS) [King et al 1999], and the Diabetes Control and Complications Trial (DCCT) demonstrated that improving HbA1c by 1% for people with type 1 diabetes *or* type 2 diabetes cuts the risk of microvascular complications by 25%. Therefore among participants with diabetes, the primary outcome of interest will also be reduction of their plasma glucoce levels. A participant will be classified as having had their plasma glucose reduced if:

1. Their HbA1c reading at month 12 is reduced to below 53 mmol/mol, or
2. Their HbA1c reading at month 12 is 5 mmol/mol below their baseline reading.

*Secondary outcomes of interest*

Secondary outcomes in this trial will include:

a) Incidence of diabetes among participants with pre-diabetes

b) Incidence of conversion from a state of pre-diabetes to normal plasma glucose levels.

c) Incidence of adverse events, including hospitalizations due to hypo- or hyperglycemia, or complications of diabetes.

d) Behavioral outcomes, including diet, physical activity, foot care, tobacco and alcohol consumption.

e) Costs of implementation of the intervention elements

f) Participant satisfaction with the individual intervention elements, including self-management

g) Differences between the country sites, in regard to baseline context infrastructure for prevention and management of T2D

h) Degree of implementation of intervention elements in each country, and differences between country sites informed by site-specific process evaluations

i) Effect of the interventions on perceptions towards diabetes, life style measures including physical activity, dietary behavior, etc.

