**Table 1: Details of tools, sources and data collection points for Part I**

| Questionnaires | Source | BL | M2-11 | EL |
| --- | --- | --- | --- | --- |
| **Eligibility & Recruitment Check** | - SMART2D | X |  |  |
| **Identification Information** | - SMART2D | X |  |  |
| **Demographic & Socioeconomic Measures** | - WHO STEPs Survey | X |  |  |
| **Medical and Medication History** | - WHO STEPs Survey  - GACD diabetes data dictionary | X |  |  |
| **Behavioural Measures – Diet** | - WHO STEPs Survey  - Summary of Diabetes Self-Care Activities (SDSCA) | X |  | X |
| **Behavioural Measures – Physical Activity** | - Summary of Diabetes Self-Care Activities (SDSCA)  - Single Question Physical Activity Questionnaire (Rose et al) <http://appliedresearch.cancer.gov/paq/q098.html> | X |  | X |
| **Behavioural Measures – Tobacco Use** | - WHO STEPs Survey | X |  | X |
| **Behavioural Measures – Alcohol Consumption** | - WHO STEPs Survey | X |  | X |
| **Other Behavioural Measures – Foot care** | - Summary of Diabetes Self-Care Activities (SDSCA) | X |  | X |
| **Biochemical – FPG^#^** | - WHO STEPs Survey | X | X |  |
| **Biochemical – HbA1c** | - WHO STEPs Survey | X |  | X |
| **Anthropometry and others: Height, weight & Waist circumference** | - WHO STEPs Survey | X |  | X |
| **Anthropometry and others: Blood Pressure** | - WHO STEPs Survey | X |  | X |
| **Anthropometry and others: 7-day pedometer steps** | - SMART2D | X |  | X |
| **Community activities §** | - Kerala Diabetes Prevention Programme |  |  | X |

^#^ FPG measurements will be used for screening in Ug & SA and interim monitoring in Ug

§ Not included in this document – to be finalised before end-line

| **SECTION 1: ELIGIBILITY & RECRUITMENT CHECK**  (Instructions: To be filled in by recruiting personnel before participants sign informed consent) | | | | |
| --- | --- | --- | --- | --- |
| **STEPs** | **Description & questions** | **RESPONSE** | | **CODE** |
|  | REDCAP: Assign the screening ID number | └──┘└──┘└──┘ | | study_id |
| **STEP 1** | **RECRUITMENT algorithm** | **No** | **Yes** |  |
|  | Does the site-specific recruitment algorithm for the screening and diagnostic tests (HbA1c or FPG) for the individual show RECRUIT? | └──┘ | └──┘ | ELI_1 |
|  | "If NO, the subject is NOT ELIGIBLE to be recruited for the trial. Do not continue with recruitment." |  |  | Inst_eli_1 |
| 🡺 If YES, proceed to STEP 2 | | | |  |

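### Text and schedules disagree on follow-up medication history, and pre-diabetes participants skip the drug questions, so a treated converter can be scored as returned to normal

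*Protocol*

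**What the plan says.** **Text of section 3.8.** The follow-up list opens with "During follow-up study visits, we will conduct the following assessments", and its first item is "Medical history assessment". The baseline list in section 3.7 uses the same label.

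**Schedules.** Table 15 in section 3.8 has a row "Medical and medication history" marked at baseline only; months 3, 6 and 12 are blank. Table 1 of the data collection tools has "Medical and Medication History" marked at baseline only, with the month 2-11 and end-line columns blank.

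**Compliance checks.** Section 3.8 has research nurses assess compliance partly by "direct questioning and pill count assessed at each monthly visit". The monthly visits are described for one group: "participants with diabetes will return to their respective cluster health facilities monthly for their clinic visits and drug refills".

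**The drug items.** Section 4 of the tools asks about insulin (G), other injectables (H), oral agents (I) and traditional or complementary medicines (J). Participants with pre-diabetes are sent straight to J. Anyone answering No to G is sent to I. The questionnaire ends for pre-diabetes before the expenditure section, which has an item on spending for diabetes medication.

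**Outcomes.** Section 3.9 lists incidence of diabetes as secondary outcome (a) and "Incidence of conversion from a state of pre-diabetes to normal plasma glucose levels" as outcome (b). It gives no rule for participants taking glucose-lowering drugs.

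**Supply.** Table 5 lists, for Uganda, "Medicines to cover stock out" among the project-provided elements of the facility strategies.

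**The concern.** Outcomes (a) and (b) are read from glucose or HbA1c, and a glucose-lowering drug lowers both. Suppose a pre-diabetes participant is diagnosed with diabetes in routine care between study visits, starts a drug, and has a normal reading at month 12. Unless the diagnosis or the drug is recorded, that person is not a case under (a) and can be a success under (b): one unfavourable event becomes one favourable event. Conversion to diabetes is also the first secondary objective in section 2.2.2.

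The text of section 3.8 would allow the drug start to be picked up. The two schedules that site staff would follow would not. Drug starts that are not recorded at the time may be hard to recover at the end of the trial.

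**Working it through.** This is mainly a comparison of passages. The protocol states no figure on this point to reproduce.

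**Step 1. Is medication history collected after baseline?** Section 3.8 text: medical history, yes. Table 15: no. Tool Table 1: no. The two schedules agree with each other and contradict the text.

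**Step 2. Does another source cover it?**

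| Source | Diabetes | Pre-diabetes |
|---|---|---|
| Monthly questioning and pill count (3.8) | Yes, as a compliance measure; no drug class or start date stated | Monthly visits not stated |
| Drug items G-I (tools, Section 4) | Baseline | Skipped even at baseline |
| Expenditure section (tools, Part III) | Given; records spending, not drugs taken | Not given |

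The expenditure timing also differs: months 3, 6 and 12 in Table 15, baseline and end-line in tool Table 3.

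**Step 3. Would interim glucose catch the conversion first?**
- Uganda: Table 15 has fasting glucose at months 3, 6 and 12. A conversion seen at one of these visits can count in the Kaplan-Meier analysis of section 3.13.2, even if glucose later falls.
- South Africa: Table 15 has the same visits, but the footnote to tool Table 1 limits interim glucose monitoring to Uganda. Coverage is uncertain.
- Sweden: HbA1c at baseline and month 12 only. A conversion treated in between can go unseen.

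**Step 4. How many people could be involved?** Inputs: annual conversion risk 10-15% (section 1.1); pre-diabetes participants per arm before the loss-to-follow-up allowance, 112, 129 and 158 (Table 16(a)). Expected converters = n x risk:
- Uganda: 112 x 0.10 = 11.2 to 112 x 0.15 = 16.8
- South Africa: 129 x 0.10 = 12.9 to 129 x 0.15 = 19.4
- Sweden: 158 x 0.10 = 15.8 to 158 x 0.15 = 23.7

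The share who would be treated and have a normal reading at month 12 is not in the documents. Assuming 25-75%, the share of an arm open to misclassification is 0.10 x 0.25 = 2.5% to 0.15 x 0.75 = 11.25%. In a Swedish arm that is 158 x 0.025 = 4 to 158 x 0.1125 = 18 people. In Uganda it is an upper limit, because interim glucose would catch some of them.

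**Step 5. Does drug supply differ by arm?** Section 3.3.3.1 states that the community arm includes the facility strategies. Planned supply is therefore the same in facility + community and facility only. It differs only against the Ugandan current-practice arm.

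**Step 6. Routing.** Because G = No leads to I, item H is never put to a participant with diabetes who says they are not on insulin.

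**The case against.** The strongest reply is that follow-up drug data are not absent. Section 3.8 lists medical history and clinical evaluation at follow-up, people with diabetes have monthly questioning and pill counts, and spending on diabetes medication is asked. The tool set shown is described as the screening and baseline set; Part IV and the process-evaluation and facility-cost forms are not shown. All of this stands. It limits the point to what is scheduled and shown, and for diabetes leaves a contradiction between text and schedule plus no stated capture of drug class or start date. It does not help pre-diabetes, where the sources shown drop out.

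A reader might infer that HbA1c differences cannot be attributed to the intervention. The documents do not support that. Covering stock-outs belongs to the facility package and is common to both facility arms, and section 3.13.1 specifies intention to treat. A drug-mediated gain is a valid effect of the assigned strategy.

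A reader might also take the fall in HbA1c among treated converters as a bias against the 3 mmol/mol target of section 3.10. A shift in one arm's mean is not a between-arm shift. The latter equals the difference in treated share between arms times the drug effect, and is zero if the shares are equal. The documents give neither quantity.

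Finally, classifying treated participants may be left to the statistical analysis plan, which is not shown. That is fair for the rule itself, but no later analysis rule can use data that the visit schedule and skip pattern prevented from being collected.

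**Conclusion.** The point holds as a conflict between section 3.8 and both schedules, with a real consequence for secondary outcomes (a) and (b) in pre-diabetes. The people at risk of misclassification are some part of roughly 11-17, 13-19 and 16-24 expected converters per arm in Uganda, South Africa and Sweden. These counts rest on the protocol's 10-15% annual risk applying to the enrolled population. That converters would be diagnosed and treated during follow-up is a reasonable inference, not something the protocol states. Exposure is greatest in Sweden, possible in South Africa depending on which schedule governs, and smallest in Uganda.

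The primary intention-to-treat comparisons are not invalidated. In the Ugandan comparison with current practice, what is lost is the ability to separate drug from non-drug contributions to the package effect. The G-to-I routing slip is a separate, minor questionnaire error. The change is worth making before enrolment.

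**What to change.** 1. Reconcile section 3.8 with Table 15 and tool Table 1 by scheduling the glucose-lowering drug items, with start date, and a question on new diabetes diagnosis since the last visit, at months 3, 6 and 12 for all participants.
2. Remove the pre-diabetes skip to J for these items; otherwise the added visits will not reach the group at issue.
3. Route G = No to H.
4. State in section 3.9 that a new diagnosis during follow-up counts as conversion under (a), and that a participant on glucose-lowering drugs at month 12 is not counted as returned to normal under (b).
5. Report drug starts by arm.

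The cost is a few questions at visits already planned, slightly longer visits, and possibly fewer participants classed as normalised.

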## 3.9 Outcomes of interest:

*Primary outcomes of interest*

Among participants with pre-diabetes, the primary outcome of interest will be reduction in plasma glucose between baseline and month 12 of follow-up. We hypothesize that participants with pre-diabetes in the facility + community arm will on average have a higher reduction in their HbA1c reading by the end of follow-up compared to participants with pre-diabetes in the facility alone arm, and the current practice arm in Uganda.

Regarding participants with type 2 diabetes, research has shown that, reduction of HbA1c level by 1% among such individuals leads to: a) 19% less likelihood of cataracts, b) 16% less likelihood of heart failure, and c) 43% less likelihood of amputations or death due to peripheral vascular disease [Anon 1993]. Further the UK Prospective Diabetes Study (UKPDS) [King et al 1999], and the Diabetes Control and Complications Trial (DCCT) demonstrated that improving HbA1c by 1% for people with type 1 diabetes *or* type 2 diabetes cuts the risk of microvascular complications by 25%. Therefore among participants with diabetes, the primary outcome of interest will also be reduction of their plasma glucoce levels. A participant will be classified as having had their plasma glucose reduced if:

1. Their HbA1c reading at month 12 is reduced to below 53 mmol/mol, or
2. Their HbA1c reading at month 12 is 5 mmol/mol below their baseline reading.

*Secondary outcomes of interest*

Secondary outcomes in this trial will include:

a) Incidence of diabetes among participants with pre-diabetes

b) Incidence of conversion from a state of pre-diabetes to normal plasma glucose levels.

c) Incidence of adverse events, including hospitalizations due to hypo- or hyperglycemia, or complications of diabetes.

d) Behavioral outcomes, including diet, physical activity, foot care, tobacco and alcohol consumption.

e) Costs of implementation of the intervention elements

f) Participant satisfaction with the individual intervention elements, including self-management

g) Differences between the country sites, in regard to baseline context infrastructure for prevention and management of T2D

h) Degree of implementation of intervention elements in each country, and differences between country sites informed by site-specific process evaluations

i) Effect of the interventions on perceptions towards diabetes, life style measures including physical activity, dietary behavior, etc.

j) Differences between the country sites, and changes within these contexts, as a result of implementing the intervention elements.

